### Participant screening and recruitment

Consecutive participants with non-specific LBP will be invited to participate in this study. The study purpose and procedures will be described to potential participants. This will include information about the benefits and potential harms of the intervention, the time required for the completion of the study, follow-up duration, voluntariness of participation, cost of participation and the rights to withdraw from the study at any point. A study information sheet will be provided to all potential participants.

If the potential participants are interested in participating, they will be screened for eligibility by a research assistant who is a physiotherapist. If the participants are found eligible, informed consent will be obtained. For those who cannot sign the consent, a witness will sign on their behalf, or the study participant will provide a thumb print on the form for those who cannot write or sign the form as per the ethical guidelines provided by Nepal Health Research Council (NHRC). We will include uneducated patients who cannot sign an informed consent in order to increase the inclusion of uneducated or low education group, given that 31% people in Nepal who are 5 years old or more cannot read and write.^37^ Additionally, exploration of feasibility of pain education in those with no schooling or low educational attainment is important in order to inform clinical practice.

Participants will be informed that they will receive one of the two treatments randomly. It will be highlighted that both of the treatment options are thought to be effective for LBP and that the goal of the main study is to compare the interventions; however, the current study will more specifically evaluate the feasibility of such a study.

### Group allocation, randomisation and blinding

Random number sequence, in random blocks of 4 and 6, will be generated using www.randomization.com, by a researcher ([name]) who is not involved in recruitment process. Allocation concealment will be performed using opaque, sealed envelopes. The participants will be allocated to one of the two groups by a hospital staff member who is not the assessor. The two groups will be: pain education group (PEG) and CG.

### Intervention

The Template for Intervention Description and Replication Checklist was followed when planning the study intervention.^38 39^ Manuals of standard operating procedures will be followed during the delivery of the interventions in both the groups. This will ensure treatment uniformity and fidelity. It is not possible to blind the intervention providers based on the design of the study.

Participants in intervention group (PEG) will receive detailed pain education as described in the next paragraph, and those in the CG will receive guideline-based physiotherapy treatment. After the completion of the post-treatment assessment at 1 week, study participants in both the groups will receive the treatment being provided by physiotherapists at Sahara Physiotherapy Hospital. Participants in both the groups will be encouraged not to seek for other medical care for LBP during the 1-week study period, unless they have to. If they do undertake other forms of treatment, they will be requested to report this during the follow-up assessment, and this will be recorded.

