#### Pain education group

The pain education will be delivered to the PEG only. We will use the pain education handouts in Nepali for Nepalese with LBP based on the resources developed by [name] and [name], called Explain Pain.^29 40 41^ It has evolved in over 15 years^42^ and undergone changes and advances.^29 40 41^
^43 44^ Pain education is delivered to provide reassurance, which means removal of fear and concerns about illness.^45^ Reassurance is among the core aspects of management of patients with non-specific problems such as LBP.^46^ Although there are no gold standard ways to provide reassurance and alleviate fear and concerns about a disease or its consequences, empathy and collaboration are thought to play important role.^47^ The Pain education intervention will be provided by the lead investigator (SS) who is trained in the delivery of this treatment and has about 10 years of experience in the management of musculoskeletal disorders, including LBP.

In order to develop the pain education resources in Nepali, the first step is the development of curriculum for pain education for patients with LBP^29^ in Nepal. The curriculum was first outlined in English (by SS) in the similar manner recommended by the developers^29^ and was reviewed and approved by both the developers (see online supplementary appendix 1). Based on the curriculum, the pain education materials and patient handouts were created (by SS) in Nepali. The clinical cases and pain stories that were compiled are actual stories collected from patients and clinicians in Nepal but will be anonymously shared to provide reasoning based on contemporary pain biology knowledge.^29^ Pictures that are found in Explain Pain resource materials^29 40 41^ were adapted in the Nepali version.

10.1136/bmjopen-2018-022423.supp1Supplementary file 1

The pain education handout and materials that are produced in Nepali is proofread and will first be pretested in 5–10 Nepalese with LBP as needed, and corrected, if necessary, before using in the feasibility study participants. The final handouts will then be printed for the use in the current study. This adapted process will ensure that the Nepali pain education materials produced are valid and culturally appropriate. However, for the purpose of the full trial, the difficulty in understanding the treatment will be assessed in the current feasibility study, and any modifications required will be made.

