#### Control group

The intervention will be provided by the physiotherapists working at the study site. Treatment integrity in the CG will be improved by providing an interactive seminar to all the physiotherapists delivering CG intervention by the lead researcher. The seminar will incorporate evidence-based information, including assessment and management of LBP based on the current recommendations from clinical practice guidelines.^23 49–51^ Research articles and simplified evidence-based summary will be provided to the physiotherapists before the interactive seminar for self-study. At the end of the seminar, a brief multiple-choice quiz will be conducted for the study physiotherapists that will assess evidence-based management of LBP. The therapists will need to score a minimum of 80% before they deliver treatment to the CG.

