Thus, the CG intervention will contain of: (1) education (advice to remain active, education about prognosis of LBP for acute LBP and avoid bed rest and braces)^23 50 51^ for 10–15 min, including time spent to listen to each participant’s pain story; (2) back massage^23 51^ for about 10 min; (3) superficial heat^23 50^ for 10–15 min; and (4) static cycling or (treadmill) walking with the aim to promote physical activity^23 50 51^ including any rest period for a total of approximately 20 min. Although superficial heat is recommended in the acute/subacute LBP,^23 50^ we included this as a common treatment for all types of LBP including chronic LBP, which could be a part of self-management. Any forms of electrotherapy and acupuncture will not be offered to the study participants.^49^ The control intervention will strictly exclude the use of pain biology education.

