6	Understanding possible contamination between the groups	Contamination between the groups will be assessed by asking all the study participants the following questions at 1 week following treatment: *1. ‘Have you talked to other participants in this study about the intervention they are receiving?’; If yes, further ask, ‘Was your attitude towards the intervention, or intervention changed after talking to one of the participants in the other group?’;* *2. ‘Are you aware of the intervention that any participants in the other group are receiving in the study?’;* *3. Are any of the participants in the other group aware of the type of intervention you are receiving in this study?’* Participants in the control group will be asked the following question: ‘*Did you read the pain education booklet or watch the video which is one of the components of the intervention group*?’ These questions are adapted from a cotwin controlled feasibility trial.^62^	The frequencies of the participants who responded affirmatively to each question will be computed separately for each treatment condition.

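### Contamination is measured only by participants' answers about other participants and the pain education materials, so pain biology content spoken by a control therapist would not be counted and the Table 4 contamination row could read 0%

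*Protocol article*

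**What the plan says.** **Delivery.** For pain education, the Protocol article states: "The Pain education intervention will be provided by the lead investigator". For the control (Control group): "The intervention will be provided by the physiotherapists working at the study site". These therapists are prepared by "providing an interactive seminar to all the physiotherapists delivering CG intervention by the lead researcher", followed by a quiz with an 80% pass mark. After the 1-week assessment (Intervention), "study participants in both the groups will receive the treatment being provided by physiotherapists at Sahara Physiotherapy Hospital". There is one study site.

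**Content rule.** "The control intervention will strictly exclude the use of pain biology education" (Intervention in the CG). The same section gives 10–15 min of the control session to education, including hearing the participant's pain story. The stated safeguard is in Intervention: "Manuals of standard operating procedures will be followed during the delivery of the interventions in both the groups".

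**Measurement.** Table 2 item 6: "Contamination between the groups will be assessed by asking all the study participants the following questions at 1 week following treatment". The questions ask whether the participant has talked with other participants, knows what the other arm receives, or is known by the other arm to receive a given treatment. Controls are also asked: "Did you read the pain education booklet or watch the video which is one of the components of the intervention group". The analysis counts affirmative answers by arm.

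**Decision rule.** Table 4 has three contamination bands: 15% or more (modify the protocol), under 15% (monitor closely) and 0% (close monitoring not needed).

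**The concern.** The item covers leakage from participant to participant, and leakage through the printed or recorded material. It does not cover leakage through the therapist. The control arm is defined partly by what its therapists must not say, and no question asks what they said. A control participant who was given a pain biology explanation would probably not recognise it as belonging to the other arm, and could truthfully answer no throughout.

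The design leaves this route open. Control sessions and the later care of pain education participants take place in one hospital's physiotherapy service, and the pain education provider trains the control therapists. Participants who have had pain education also hold a handout and, where they have the means to use it, an audio-recording.

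At stake is the contamination row of Table 4. If verbal drift occurred, the row could still fall in its most favourable band, and a full trial on the same model would inherit a weaker contrast between arms without warning. By the protocol's own argument small amounts may matter. Its dosage section for pain education cites lasting reassurance from interventions as short as 5 min, and the control education slot is two to three times that length.

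**Working it through.** The plan gives no figure to reproduce here. The check compares the route with the instrument, then looks at timing and the threshold.

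**1. Would any planned measure register verbal pain biology content in a control session?**
- Table 2 item 6, talking to other participants: no.
- Item 6, the two awareness questions: only if the therapist described the content as the other arm's treatment.
- Item 6, booklet or video: only if material was passed on, not if it was explained aloud. (The home advice section describes a handout and an audio-recording, not a video.)
- Item 4, weekly interview of physiotherapists: it concerns screening and recruitment.
- Item 8, adherence: it records home treatment and deviations from it.
- Items 10 and 11: they ask how hard the information was to understand, not what it was.

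If every control session had drifted verbally, the item 6 count could still be 0 of 20.

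**2. Could post-week-1 care of pain education participants overlap with later control sessions?** The inputs are 40 participants, 20 per arm, blocks of 4 and 6, and care passing to site physiotherapists after 1 week. No accrual rate is planned. The 2–3 and 4 or more per week are Table 4 bands, and 8 per week is an added fast case. Steady accrual is assumed.

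With rate r per week and lag L weeks, the share of controls randomised after the first pain education participant could have moved to site care is roughly 1 − rL/40. A simulation with the stated block sizes (20,000 runs per case) refines this:

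| r per week | Weeks to recruit (40/r) | L = 1: approx. / simulated | L = 2: approx. / simulated |
|---|---|---|---|
| 2 | 20 | 95% / 94.0% | 90% / 88.5% |
| 3 | 13.3 | 92.5% / 91.3% | 85% / 83.2% |
| 4 | 10 | 90% / 88.5% | 80% / 78.2% |
| 8 | 5 | 80% / 78.2% | 60% / 58.2% |

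Most control sessions would fall inside the window in every case. These are shares with an opportunity for overlap, not rates of contamination.

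**3. What does the threshold mean in counts?** 0.15 × 20 = 3 controls, and 0.15 × 40 = 6 participants. Three affected controls are 3/20 = 15% (modify) on one denominator and 3/40 = 7.5% (monitor closely) on the other. Table 4 does not say which applies.

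**The case against.** The strongest reply has four parts.

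- **The chain is conjectural.** A patient after one session would have to convey the ideas to a physiotherapist, who would then have to depart from a manualised control. None of this is shown. The training route is weak too: the seminar covers guideline recommendations and is meant to protect the control. This stands, and limits the claim to a possible route that is not measured.
- **The same therapists are not named.** A reader might infer that the physiotherapists who deliver the control also take over pain education participants. The article says only that both activities belong to physiotherapists at the one hospital. It gives no staffing numbers or division of patients. This also stands.
- **The article is condensed.** The operating manuals are not shown and may contain session logs, so one cannot say that fidelity goes unchecked altogether. That is fair. The point does not depend on it, because Table 2 itself fixes how this primary objective is assessed and Table 4 fixes how it is judged. A log elsewhere would not enter either as written.
- **One row does not decide.** A reader might infer that 0% contamination sends the trial forward unmodified. It does not: contamination is one of eight Table 4 rows, and this study makes no efficacy claim. The effect is confined to that row.

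The item is also not blind to every therapist route, since the booklet question could catch shared material. Spoken explanation is what it misses.

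**Conclusion.** The point holds as a defect in a stated measure. Contamination is a primary feasibility objective, and its instrument cannot see spoken pain biology content in control sessions, although the protocol strictly excludes that content and its single-site arrangement leaves a route for it. The contamination row can therefore read 0%, with close monitoring judged unnecessary on that criterion, whatever control therapists said.

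The size of any drift cannot be estimated from the documents. What can be sized is the opportunity (roughly 58% to 94% of controls, under steady accrual at 2 to 8 per week with a 1- or 2-week lag) and the threshold (3 of 20 controls or 6 of 40 participants). The opportunity figures also assume that the physiotherapists giving later care can influence control sessions, whether by being the same people or by working alongside them. Care after week 1 cannot alter that participant's own 1-week data; the route runs only to controls treated later. The change is worth making before recruitment because it is cheap and detecting such problems is the purpose of a feasibility trial.

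**What to change.** 1. **Therapist record.** Add to Table 2 item 6 a brief form that the treating physiotherapist completes after each control session: components delivered, topics explained in the education part, and whether any pain education material had been seen. Word it neutrally and leave the topics open. A checklist naming pain biology, metaphors or stories could cue therapists to the content they must avoid.
2. **Participant question.** At 1 week, ask controls what the therapist explained about the cause of their pain. Place it after the outcome measures and the assessor's allocation guess have been recorded, because the answer may reveal the arm.
3. **Coding and counting.** Have someone other than the treating therapist code both sources against the key concepts of the pain education curriculum. Count a control session with pain biology content as contamination in Table 4.
4. **Denominator.** State it, for example controls treated, so that 3 of 20 is 15%.

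The cost is about a minute for each of 20 control sessions, one extra question per control, and a small coding task. Self-report by the therapists being checked may understate drift; the participant question offsets this only in part. Separate rostering of therapists is not recommended here, because staffing is not described and its cost cannot be judged.

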#### Pain education group

The pain education will be delivered to the PEG only. We will use the pain education handouts in Nepali for Nepalese with LBP based on the resources developed by [name] and [name], called Explain Pain.^29 40 41^ It has evolved in over 15 years^42^ and undergone changes and advances.^29 40 41^
^43 44^ Pain education is delivered to provide reassurance, which means removal of fear and concerns about illness.^45^ Reassurance is among the core aspects of management of patients with non-specific problems such as LBP.^46^ Although there are no gold standard ways to provide reassurance and alleviate fear and concerns about a disease or its consequences, empathy and collaboration are thought to play important role.^47^ The Pain education intervention will be provided by the lead investigator (SS) who is trained in the delivery of this treatment and has about 10 years of experience in the management of musculoskeletal disorders, including LBP.

In order to develop the pain education resources in Nepali, the first step is the development of curriculum for pain education for patients with LBP^29^ in Nepal. The curriculum was first outlined in English (by SS) in the similar manner recommended by the developers^29^ and was reviewed and approved by both the developers (see online supplementary appendix 1). Based on the curriculum, the pain education materials and patient handouts were created (by SS) in Nepali. The clinical cases and pain stories that were compiled are actual stories collected from patients and clinicians in Nepal but will be anonymously shared to provide reasoning based on contemporary pain biology knowledge.^29^ Pictures that are found in Explain Pain resource materials^29 40 41^ were adapted in the Nepali version.

10.1136/bmjopen-2018-022423.supp1Supplementary file 1

The pain education handout and materials that are produced in Nepali is proofread and will first be pretested in 5–10 Nepalese with LBP as needed, and corrected, if necessary, before using in the feasibility study participants. The final handouts will then be printed for the use in the current study. This adapted process will ensure that the Nepali pain education materials produced are valid and culturally appropriate. However, for the purpose of the full trial, the difficulty in understanding the treatment will be assessed in the current feasibility study, and any modifications required will be made.

#### Dosage of the PEG intervention

A single approximately 1 hour pain education will be delivered to the PEG, because evidence indicates that: (1) interventions as brief as 5 min have been shown to have reassuring effects lasting for up to a year,^44^ and a single consultation has been found to be as reassuring as the multiple session interventions.^47^ We prefer a single session treatment over multiple session treatment, because for many patients in rural Nepal, it is difficult to deliver a multiple session treatment in reality. Thus, we plan to provide a single session delivering key concepts of Explain Pain, which will be reinforced by providing patient handouts to look at and read at home. In fact, a 1-hour session should be adequate to cover the key Explain Pain concepts by keeping the content simple and jargon free. Use of a plain language in the health-related education is important to adapt in low health literacy.^48^

#### Home advice for PEG group

A printed handout of the pain education material will be provided only to the study participants in the PEG. Participants will be advised to read them, and perform physical activity including walking for approximately 30 min. Education accompanied by written information has been reported to yield the largest effects on fear component of emotional distress.^47^ However, education level of Nepalese is low (65%); 37 we will adapt the written materials to incorporate many more images than text.

For those who cannot read, the family member(s) will be encouraged to read out the materials to them. To complement the written materials, we will also provide an audio-recording of the pain education session to the patients as an online URL link to Nepali patient education material stored in the cloud or will be copied to their smart phones or both for those who have the facilities to use them. The pain education advice will be directed towards reducing brain’s perception of movement and exercise as a threat encouraging participants to slowly pace the movement, physical activity and exercise. This is thought to desensitise the sensitive nervous system and improve function. A written instruction to perform general exercises and physical activity will be sent to the participants. Participants will be discouraged to use a lumbar corset and rest as coping strategy, whereas physical activity and return to work will be encouraged. A reminder to perform home exercises will be sent to all participants for a total of 5 days in the week.

#### Control group

The intervention will be provided by the physiotherapists working at the study site. Treatment integrity in the CG will be improved by providing an interactive seminar to all the physiotherapists delivering CG intervention by the lead researcher. The seminar will incorporate evidence-based information, including assessment and management of LBP based on the current recommendations from clinical practice guidelines.^23 49–51^ Research articles and simplified evidence-based summary will be provided to the physiotherapists before the interactive seminar for self-study. At the end of the seminar, a brief multiple-choice quiz will be conducted for the study physiotherapists that will assess evidence-based management of LBP. The therapists will need to score a minimum of 80% before they deliver treatment to the CG.

